### 1.5. Time-Dependent Diffusion MRI

Time-dependent diffusion (TDD) MRI is a relatively new sequence that probes water molecule diffusivity over short diffusion times, potentially revealing the tissue microstructure beyond single-cell resolution. Early animal studies demonstrated sensitivity to microscopic tumor features [16,17,18,19]; however, clinical adoption was limited by the need for very high gradient strengths [20,21].

Recent pilot studies on head and neck, breast, and prostate cancers demonstrated technical feasibility even with limited diffusion time ranges [22,23,24,25]. Using high-performance gradients (≤80 mT/m), Xu et al. advanced biophysical modeling to extract quantitative microstructural maps from TDD data; however, this approach was not yet feasible for routine diagnostics [23,26]. A breakthrough was achieved when Wu et al. showed that standard clinical MRI systems could acquire TDD images that distinguished csPCa from non-csPCa, exploiting the stronger diffusion-time dependence observed in highly cellular, high-grade tumors [27]. This line of research advances the concept of virtual prostate pathology using non-invasive imaging methods.

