### 2.7. Histopathologic Analysis

The interval between MRI examination and prostate biopsy will be limited to 30 days. All biopsy specimens will be interpreted by senior pathologists with over 10 years of experience, following the International Society of Urological Pathology (ISUP) grading standards [48]. The GSs of all tumor foci will be recorded and the findings grouped into five categories according to the ISUP grade groups (GGs): GS 3+3 (GG 1), GS 3+4 (GG 2), GS 4+3 (GG 3), GS 4+4 (GG 4), and GS over 4+4 (GG 5). For analysis purposes, benign lesions and PCa GG 1 will be classified as non-clinically significant prostate cancer (non-csPCa), while lesions within GGs 2–5 will be classified as csPCa. To link imaging findings to the reference standard, MRI-visible targets (index lesion and any additional PI-RADS ≥ 3 lesions) will be contoured and assigned standardized lesion identifiers and location labels. During MRI-guided biopsy, each targeted core will be recorded with the corresponding lesion identifier, enabling a core-level linkage between MRI targets and histopathology. When multiple targeted cores are obtained for a lesion (and when systematic cores are also available), the lesion-level classification will be determined using the highest ISUP grade group among the cores assigned to that MRI target, with predefined rules to adjudicate discordant or multifocal findings. Among csPCa cases, we will report the distribution of ISUP grade groups (1–5) and summarize lesion-level grade where applicable. Among non-csPCa participants, we will report alternative diagnoses, including benign histology and ISUP 1 (non-clinically significant cancer), and any other relevant findings (e.g., prostatitis/benign prostatic hyperplasia) when available.

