### 2.9. Statistical Analysis

Microstructural parameters will be measured within manually delineated lesion ROIs, excluding boundary voxels to minimize partial-volume effects. In addition to mean values, we will compute a small prespecified set of alternative ROI summary statistics (e.g., median, selected percentiles, and dispersion metrics), with any feature-set selection performed strictly within the training data to avoid optimistic bias.

Post hoc comparisons among tissue categories (benign tissue and ISUP grade groups) will be performed using one-way ANOVA (or the Kruskal–Wallis test if assumptions are violated), followed by multiplicity-adjusted pairwise testing. Analyses will be conducted using RStudio (Version IDE 2026.01.0) and IBM SPSS Statistics (Version 31.0.1.0) software.

Diagnostic performance will be evaluated in the biopsy-verified PI-RADS 3–4 cohort (csPCa defined as ISUP ≥ 2). We will train and compare LDA, SVM, Random Forest, and XGBoost, selected to represent linear, margin-based, and ensemble tree-based approaches with different bias–variance trade-offs, using patient-level, stratified fivefold cross-validation with all pre-processing and hyperparameter tuning performed within training folds only. Model selection will be prespecified and specificity-driven. Among candidate classifiers, we will prioritize the approach that maximizes specificity for non-csPCa within the PI-RADS 3–4 cohort, while maintaining sensitivity above a prespecified minimum for csPCa. The upgrade and downgrade thresholds will be determined within training folds only using this prespecified criterion, then locked and applied unchanged to the held-out/prospective evaluation cohort. Performance will be reported with 95% confidence intervals.

PROS-TD-AI will output two continuous risk scores: an upgrade risk (0–1) for PI-RADS 3 cases (likelihood that the case should be managed as PI-RADS 4/csPCa-likely), and a downgrade risk (0–1) for PI-RADS 4 cases (likelihood that the case should be managed as PI-RADS 3/non-csPCa-likely). Prespecified, locked thresholds (the prespecified upgrade cutoff and the prespecified downgrade cutoff) will map these scores to a binary recommendation within the PI-RADS 3–4 decision zone (final recommendation: “3” vs. “4”), corresponding to non-csPCa-likely versus csPCa-likely classification in this subgroup.

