The primary endpoint is the paired improvement in specificity (non-csPCa correctly recommended as “3”) of PROS-TD-AI-assisted recommendations versus standard PI-RADS (4 vs. 3), tested using McNemar’s test [49], in the non-csPCa subgroup (two-sided alpha = 0.01). The secondary endpoints include paired sensitivity in csPCa (McNemar), upgrade/downgrade reclassification rates stratified by pathology, and continuous-score discrimination (ROC AUC) and calibration (*p* < 0.05 for secondary analyses). We will present 2 × 2 cross-tabulations (index test vs. reference standard) for PI-RADS and PROS-TD-AI recommendations in the biopsy-verified PI-RADS 3–4 cohort, including counts of TP, FP, TN, and FN. Baseline demographic, clinical, and technical characteristics will be summarized for each analysis split (training/validation/test and the prospective evaluation cohort) to assess representativeness and potential distribution shift, including age, PSA/PSA density, prostate volume, PI-RADS category, and key acquisition variables (scanner/vendor and sequence quality markers). Because participants are consecutively enrolled within the routine intended-use pathway (biopsy-verified PI-RADS 3–4), we expect the csPCa prevalence to reflect this clinical setting. We will report the observed csPCa prevalence and discuss any material deviation as potential spectrum effects affecting generalizability.

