### 2.10. Sample Size Calculation

The primary endpoint is the within-participant difference in specificity for detecting clinically significant prostate cancer (csPCa; ISUP ≥ 2) within the PI-RADS 3–4 decision zone, comparing standard PI-RADS v2.1 assessment (test-positive defined as PI-RADS 4; test-negative as PI-RADS 3) versus the PROS-TD-AI-assisted recommendation (positive = “recommend 4”; negative = “recommend 3”). All eligible PI-RADS 3–4 examinations will undergo MRI-targeted biopsy (±systematic biopsy per local protocol) within a prespecified time window, providing complete histopathological verification for the primary analysis. We powered this study to detect an absolute specificity improvement of 0.10 (two-sided alpha = 0.01; 80% power) using a paired-proportions (McNemar) approach applied to the non-csPCa subgroup. Let p10 denote the proportion of non-csPCa participants classified as positive by PI-RADS (4) but negative by PROS-TD-AI (3) (false-positive→true-negative), and p01 denote the reverse discordance. Under conservative, prespecified discordant-pair assumptions (p10 = 0.15; p01 = 0.05; net delta = p10 − p01 = 0.10; total discordance = p10 + p01 = 0.20), the required number of non-csPCa participants is computed as follows: n_non-csPCa = ((z_(1−alpha/2) + z_(1−beta))^2^ × (p01 + p10))/(p10 − p01)^2^. Using z_(1−alpha/2) = 2.576 and z_(1−beta) = 0.842 gives n_non-csPCa ≈ ((2.576 + 0.842)^2^ × 0.20)/0.10^2^ ≈ 234 [49]. To convert this to the total sample size, we used the PROMIS trial as an external prevalence benchmark; PROMIS reported 220/576 = 38% (95% CI 34–42) clinically significant cancer on template mapping biopsy [6]. For conservative planning, we assumed 38% (the proportion of ISUP csPCa, thus 62% non-csPCa), yielding N_total = 234/0.62 ≈ 378 PI-RADS 3–4 participants. We will inflate this by 10–15% for exclusions and non-evaluable examinations, resulting in a planned enrollment of approximately 420–445 participants (target ~450). This target also satisfies empiric minimum sample sizes proposed for objective testing of AI binary classification performance metrics (including ROC AUC), where an empirical minimum sufficient test sample size of approximately 400 studies has been reported [50].

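### The tissue-category comparison uses only unordered tests on an ordered grade scale; adding a one-degree-of-freedom ordered test would be a cheap, low-severity improvement

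*Protocol article*

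**What the plan says.** Section 2.9 of the protocol article states: "Post hoc comparisons among tissue categories (benign tissue and ISUP grade groups) will be performed using one-way ANOVA (or the Kruskal–Wallis test if assumptions are" not met). The step after that is given as "followed by multiplicity-adjusted pairwise testing". The section names no trend test, ordered contrast or estimate of change per grade.

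The scale comes from section 2.7, which has "the findings grouped into five categories according to the ISUP grade groups (GGs") in order of rising Gleason score. With benign tissue that makes six categories. The same section also sets a binary cut: "lesions within GGs 2–5 will be classified as csPCa", with benign tissue and GG 1 on the other side.

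The reason to expect a direction is in section 1.5, which describes earlier work as "exploiting the stronger diffusion-time dependence observed in highly cellular, high-grade tumors". Section 1.2 links ISUP grade 2 or above to high cellularity.

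No significance level is attached to the tissue-category comparison. Section 2.9 gives "< 0.05 for secondary analyses" in its account of the secondary endpoints, but this comparison is not among those endpoints.

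**The concern.** One-way ANOVA and Kruskal–Wallis treat the six categories as exchangeable labels. Permuting the grade labels would leave the omnibus result unchanged. The test is spread over five degrees of freedom, whereas a steady rise or fall with grade can be captured with one.

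The pairwise follow-up shows which categories differ, but it involves up to 6 × 5 / 2 = 15 adjusted contrasts, some between groups that may be small. It does not pool evidence along the scale.

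A real graded relation of moderate size could therefore be reported as not significant, and the plan would yield no estimate of how a parameter changes per grade step. What is at stake is the descriptive evidence that the microstructural parameters track grade. The diagnostic-accuracy comparison is not at stake.

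**Working it through.** **The plan's own figures.** Section 2.10 powers only the McNemar test ("two-sided alpha = 0.01; 80% power"). (2.576 + 0.842)² × 0.20 / 0.10² = 233.7, rounded up to 234; 234 / 0.62 = 377.4, rounded up to 378; 378 / 0.90 = 420 and 378 / 0.85 = 444.7, rounded up to 445. These reproduce. No power, effect size or SD is given for the tissue comparison, so what follows rests on assumptions.

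**Assumptions.** N = 378, one lesion per participant; 38% csPCa (section 2.10); six groups; alpha 0.05. Base group sizes, benign to GG 5, are 151/83/76/38/15/15. These sum to 378, with 144 (38%) in GG 2–5. Scores run from 0 to 5.

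**Method.** ANOVA power comes from the noncentral F distribution with 5 and 372 df and noncentrality λ. The linear contrast uses 1 and 372 df and noncentrality λ × r², where r² is the squared weighted correlation between the mean profile and the scores. For an exactly linear profile r² = 1.

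**Linear gradient.**

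| λ | Trend power | ANOVA power | Difference (points) |
|---|---|---|---|
| 3.86 | 50% | 28% | 22 |
| 4.92 | 60% | 35% | 25 |
| 6.20 | 70% | 44% | 26 |
| 7.89 | 80% | 55% | 25 |
| 10.56 | 90% | 70% | 20 |
| 13.06 | 95% | 80% | 15 |
| 18.47 | 99% | 93% | 6 |

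So the gain is 15 to 26 points while trend power lies between 50% and 95%. It shrinks for stronger and for very weak effects.

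**Rank versions (simulation, base mix).** Kruskal–Wallis against a Spearman trend test gives 47% against 72% at 0.10 SD per grade step, and 71% against 89% at 0.127 SD. A second assumed mix (42/20/19/10/5/4%) gives 50% against 73% at 0.10 SD and 71% against 88% at 0.12 SD.

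**Step at GG 2 (the protocol's own cut).** In the base mix the mean score is 484/378 = 1.280 and its variance 1.916. The csPCa share is 144/378 = 0.381, with mean score 401/144 = 2.785. The covariance is 0.381 × (2.785 − 1.280) = 0.573 and the step variance 0.381 × 0.619 = 0.236, so r² = 0.573² / (1.916 × 0.236) = 0.73. Where ANOVA has 80% power (λ = 13.02), the trend test has about 87%; across assumed mixes, 85 to 87%. Where ANOVA has 60%, the trend test has 68 to 72%. The gain is 5 to 12 points.

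**Shapes that go the other way.**
- Only GG 4–5 differ: r² = 0.47 in the base mix, so about 69% against 80% for ANOVA (64 to 72% across assumed mixes).
- Only cancer versus benign differs: r² = 0.57, so about 77% against 80% (69 to 82% across mixes).
- Rise then fall: 5 to 56% against 60% for ANOVA.

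**Pairwise follow-up (base mix, linear, Bonferroni over 15 pairs).** At 0.127 SD per step the best-powered pair, benign against GG 5, has 27% power. The chance that any pair is significant is 55%, against 93% for the linear contrast. At 0.10 SD it is 33% against 77%. The pairwise tests do not recover the loss when the gradient is linear.

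**The case against.** The strongest reply is that nothing here is wrong. ANOVA or Kruskal–Wallis with adjusted pairwise tests controls type I error, shows which categories differ and can pick up non-monotone patterns. The comparison is labelled post hoc, is not a listed endpoint and carries no power claim. All of that stands.

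Three stronger readings are tempting, and the protocol supports none of them.

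- *That the protocol expects a grade-by-grade gradient.* The phrase in section 1.5 belongs to a background sentence about separating csPCa from non-csPCa. Section 1.2 ties high cellularity to ISUP 2 or above, and the endpoints use the cut at GG 2. No section hypothesises a monotone change from GG 1 to GG 5 or a direction for each parameter. What remains is an ordered scale and a directional rationale, which is enough to justify adding an ordered test.
- *That the plan forfeits 15 to 26 points of power.* That needs a near-linear relation of moderate size and an assumed grade mix. For a step at GG 2 the figure is 5 to 12 points.
- *That the trend test should replace or lead the omnibus test.* With no shape given, that would build in an assumption that can cost power.

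The sample is also uncertain. The tissue comparison is not expressly limited to PI-RADS 3–4; PI-RADS 5 patients are also biopsied and additional lesions contoured, so N and the high-grade share could exceed those assumed.

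It might be said that a trend contrast is a detail for an analysis plan not shown. But the article names its tests for this comparison, and neither omnibus test uses the order.

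**Conclusion.** The point holds as a low-severity improvement. Section 2.9 fixes unordered tests for an ordered scale with a directional rationale, and an ordered test alongside them would add power for monotone relations and supply an estimate of change with grade.

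The size depends on assumptions that the protocol cannot confirm (378 lesions, 38% csPCa, six groups, alpha 0.05, an assumed grade mix): about 15 to 26 points for a linear gradient of moderate size and 5 to 12 points for a step at GG 2. There is a loss if only GG 4–5 differ or the pattern is non-monotone, and possibly if only cancer versus benign differs. The planned tests remain valid. The primary McNemar test, the sample size and the secondary endpoints listed in section 2.9 are untouched.

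**What to change.** In section 2.9, keep the ANOVA/Kruskal–Wallis and adjusted pairwise tests and prespecify beside them, for each microstructural parameter, a one-degree-of-freedom ordered test across benign < GG 1 < GG 2 < GG 3 < GG 4 < GG 5. Use a linear contrast, or Jonckheere–Terpstra or Spearman if the ANOVA assumptions fail, and report the slope or rank correlation with its 95% CI.

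This takes one sentence and a few lines of code, with no new data or participants. The downside is one additional test per parameter, which assumes a roughly monotone relation; the retained unordered tests cover the case where it is not. Writing it in before results are seen avoids a data-driven choice of test.

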### 1.7. Deep Learning-Based Interpretation

Accurate lesion localization is essential because the peripheral and transition zones of the prostate differ markedly in architecture and cancer prevalence [30]. Advances in deep learning (DL) have enabled automated zone segmentation on both mpMRI and transrectal ultrasound, making zone-specific assessment feasible in routine practice [31,32].

Therefore, future work should evaluate zone-specific diagnostic performance of TDD-derived microstructural parameters and test machine learning algorithms for imaging-based PCa risk estimation, particularly given that reproducibility remains hampered by high inter-observer variability [33]. Within the standard diagnostic workflow, novel imaging techniques aim to reduce unnecessary biopsies by offering accurate and non-invasive detection of csPCa [34].

Accordingly, this study will prospectively assess the diagnostic contribution of TDD-derived imaging metrics integrated into an AI-based interpretation framework by comparing their performance in predicting csPCa against PI-RADS v2.1-driven mpMRI in real-world clinical practice. In line with this, the primary objective is to evaluate whether the AI-enhanced TDD-MRI pipeline (PROS-TD-AI) improves the classification of clinically significant prostate cancer (csPCa; ISUP grade group ≥ 2) within the PI-RADS 3–4 decision zone compared with standard PI-RADS v2.1 (with the primary endpoint being the paired specificity improvement for csPCa classification). The secondary objectives are as follows: (1) to develop and evaluate an automated prostate segmentation model (reporting the Dice similarity coefficient); (2) estimate TDD microstructural parameters and perform lesion/tissue classification (reporting AUC, accuracy, sensitivity, and specificity with 95% CIs); and (3) assess the integrated end-to-end PROS-TD-AI pipeline combining imaging and clinical features, including robustness and failure modes.

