### 2.6. Radiological Imaging Analysis

All standard mpMRI examinations (excluding the TDD sequence) will be interpreted according to PI-RADS v2.1 by radiologists through PACS. After signing the report, the radiologist will segment the index lesion and any additional PI-RADS 3-4 lesions within one month, blinded to biopsy results. These segmented regions will define the ROIs for extracting microstructural parameters from co-registered TDD images. TDD-derived maps will not be displayed during lesion contouring.

Microstructural parameters—including intracellular volume fraction (v***_in_***), cell diameter (***d***), extracellular diffusivity (***D_ex_***), and cellularity index (v***_in_/d***)—will be estimated using Microstructure Estimation Transformer with Sparse Coding (METSC) [47], a transformer-based architecture designed for multi-shell diffusion MRI. METSC addresses limitations of conventional non-linear optimization in biophysical multi-compartment models by learning latent representations directly from q-space samples. This approach reduces the number of diffusion encodings required, demonstrating reduced scan times while preserving or improving fitting accuracy.

TDD-derived microstructural metrics obtained using METSC will be evaluated for their ability to classify lesion categories and will contribute to the training and validation of the PROS-TD-AI framework.

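### Tissue-category comparisons use one-way ANOVA or Kruskal–Wallis on lesion ROIs, although one man can contribute several lesions, so their p-values can be miscalibrated

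*Protocol article*

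**What the plan says.** Section 2.9 sets the unit of measurement: "Microstructural parameters will be measured within manually delineated lesion ROIs". It then describes "Post hoc comparisons among tissue categories (benign tissue and ISUP grade groups"), which "will be performed using one-way ANOVA (or the Kruskal–Wallis test if assumptions are violated), followed by multiplicity-adjusted pairwise testing".

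Section 2.6 shows that a man can have more than one such ROI: "the radiologist will segment the index lesion and any additional PI-RADS 3-4 lesions within one month, blinded to biopsy results". It continues: "These segmented regions will define the ROIs for extracting microstructural parameters from co-registered TDD images".

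Section 2.7 puts the grouping variable at the same level. There, "MRI-visible targets (index lesion and any additional PI-RADS ≥ 3 lesions) will be contoured and assigned standardized lesion identifiers and location labels", and each target takes the highest ISUP grade group among the cores assigned to it. (Section 2.6 names PI-RADS 3–4 for the additional lesions and section 2.7 names PI-RADS 3 or higher. Under either wording several ROIs per man are possible.)

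The only safeguard stated for dependence within a patient is in sections 2.5.4, 2.9 and 2.11: data are split by patient, and all of a patient's lesions stay in one cross-validation fold. For the tissue comparisons the article states no mixed model, GEE, cluster bootstrap or rule of one lesion per man.

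**The concern.** One-way ANOVA and Kruskal–Wallis both treat each observation as independent. Two ROIs from the same man share the scan session, motion, fit quality and biology, so their parameter values are likely to be correlated. Kruskal–Wallis relaxes the distributional assumption only. If the independence assumption is the one that fails, the stated fallback fails with it.

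Keeping a patient's lesions in one fold prevents leakage in model development. It does nothing for the standard errors or p-values of a group comparison. The plan thus recognises the clustering in one place and names a test that ignores it in another.

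At stake are the p-values for whether the diffusion parameters differ between benign tissue and the ISUP grade groups. These comparisons are post hoc and are not among the secondary endpoints listed in section 2.9, but they are the plan's direct test of whether the parameters track tissue grade.

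**Working it through.** **1. The plan's own figure.** The article gives no figure for the tissue comparisons, only for the primary test (section 2.10). That figure reproduces: (2.576 + 0.842)² × 0.20 / 0.10² = 233.7, rounded to 234 non-csPCa participants. Then 234/0.62 = 377.4, rounded to 378, and 378/0.90 = 420 and 378/0.85 = 445. All of these count participants, so the point made here does not change them.

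**2. Inputs for the check.**
- From the document: 378 participants (section 2.10), and a nominal level of 0.05 (the secondary-analysis level in section 2.9, assumed to apply because the tissue comparisons have no level of their own).
- Assumed, because the document is silent: share of men with two lesions (20%, 40%, 100%), ICC of the metric within a man (0.3, 0.6), and six categories (benign and grade groups 1–5) with proportions 0.45, 0.17, 0.20, 0.10, 0.05 and 0.03.

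**3. Simulated rejection under no true difference.** Normal outcomes, 2,000 datasets per setting. The Monte Carlo standard error at 5% is √(0.05 × 0.95/2000) ≈ 0.005.

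| Second lesion's category | Men with two lesions | ANOVA, ICC 0.3 | ANOVA, ICC 0.6 |
|---|---|---|---|
| same as the first | 20% | 0.074 | 0.102 |
| same as the first | 40% | 0.095 | 0.142 |
| same as the first | 100% | 0.142 | 0.235 |
| same in half, random in the rest | 20% | 0.066 | 0.067 |
| same in half, random in the rest | 40% | 0.064 | 0.085 |
| unrelated to the first | 20–100% | 0.052–0.059 | 0.049–0.054 |

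Kruskal–Wallis gave nearly the same values: 0.071 to 0.227 over the same-category rows.

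**4. Check by formula.** If a share s of men has two same-category lesions, the ROI-weighted cluster size is m = (1 − s + 4s)/(1 + s), and the between-group statistic is inflated by about D = 1 + (m − 1) × ICC. With six groups (5 degrees of freedom, 5% point 11.07), the true size is about P(χ²₅ > 11.07/D).
- s = 0.2: m = 1.6/1.2 = 1.333. ICC 0.3 gives D = 1.10 and size 0.073. ICC 0.6 gives D = 1.20 and size 0.100.
- s = 0.4: m = 2.2/1.4 = 1.571. ICC 0.3 gives D = 1.171 and size 0.092. ICC 0.6 gives D = 1.343 and size 0.143.

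These agree with the simulation. A separate simulation with three categories and 1/2/3 lesions in 60/30/10% of men (assumed), all of one category within a man, gave 0.086 at ICC 0.3 and 0.116 at ICC 0.5.

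**5. Opposite direction.** If each man supplies one benign and one tumour ROI and the two groups are compared as independent, the true variance of the difference is smaller than the test assumes by the factor 1 − ICC. In 4,000 datasets of 200 men the size fell to 0.021 (ICC 0.3) and 0.001 (ICC 0.6). This shows the direction only. The plan does not describe such a design.

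**The case against.** The strongest reply is that the article does not fix the unit of analysis. Section 2.9 does not say that each ROI enters as a separate observation, section 2.3 defines evaluability by the index lesion, and section 2.7 refers to predefined rules for multifocal findings that are not reproduced. A full protocol or SAP could hold a rule of one lesion per man. That is possible, but the article is not silent here. It names the tests, makes the lesion ROI the measured unit and labels histology by lesion. Those statements together do not fit.

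The second reply is about size, and it stands. The larger rejection rates need many multi-lesion men and concordant grades within a man. With a mean of 1.2 lesions per man, a simple two-sided test of one contrast with design effect 1 + 0.2 × ICC moves 0.05 only to 0.052–0.066 for ICC 0.1–0.7. A mixture of concordant and discordant lesions would partly offset.

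A reader might also infer three stronger things that the document does not support:
- **That the lesion-level confidence intervals are wrong.** Section 1.7 plans to "perform lesion/tissue classification (reporting AUC, accuracy, sensitivity, and specificity with 95% CIs"), but no interval method is named. They would be wrong only if lesions were treated as independent, which the article does not say.
- **That secondary objective 2 rests on these tests.** That objective is reported as AUC, accuracy, sensitivity and specificity, none of which comes from the ANOVA, and no feature-selection rule uses its p-values.
- **That every man supplies a benign reference ROI, so that a pairing is wasted.** Only MRI-visible targets are contoured. Benign and tumour ROIs from one man would arise mainly in multi-lesion men with discordant histology.

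**Conclusion.** The point holds for the post hoc tissue comparisons. The stated tests assume independence, the described data do not guarantee it, and the stated fallback shares the assumption. The p-values can be miscalibrated, in a direction and by an amount that the document does not determine. Under the assumed range (20–40% of men with two same-category lesions, ICC 0.3–0.6) a nominal 5% ANOVA rejects about 7–14%. With unrelated categories within a man it stays near 5%, and with benign and tumour ROIs from the same man it falls below 5%. It would therefore be wrong to say that the tests are too liberal as a rule.

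The primary McNemar comparison, its alpha and the sample size count participants and are untouched. This is a mismatch in a secondary, post hoc analysis, worth correcting because the repair is cheap.

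**What to change.** In section 2.9, replace the one-way ANOVA/Kruskal–Wallis sentence with a linear mixed model for each microstructural parameter: tissue category as fixed effect, a random patient intercept, and a transformed outcome if the residuals are skewed. Keep the multiplicity-adjusted pairwise contrasts as planned. GEE clustered on patient would serve equally, as would one prespecified lesion per man if the sponsor prefers to keep the simple tests. State the unit of analysis, and report the number of lesions per man.

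Where lesion-level AUC, accuracy, sensitivity or specificity is reported, add that the 95% intervals are obtained by resampling patients rather than lesions.

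The cost is a change of wording and a few lines of code in the R environment already named in that section. No new data, recruitment or change to the primary analysis is needed. Some p-values and secondary intervals will move, in either direction.
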